#### **Outcome variables: Primary outcomes**

1. 30 Meter Sprint Test
2. Agility T-Test

The gathered information will be condensed to produce baseline characteristics based on demographic factors. Continuous variables will be represented by mean and standard deviation; categorical variables will be represented by frequency and percentage. The continuous variables will be tabulated with the mean, standard deviation, standard error, minimum, maximum, and confidence interval (CI) at 95% for parametric data after being compared to the outcome variables with a 5% significance level ( $P \leq 0.05$ ), data from all continuous outcome variables will be tested using a normality test called Kolmogorov-Smirnov test. Non-parametric tests will be used to assess significance if the null hypothesis of normality is rejected, implying that the data is not normal. The significant difference will be at a 5% level ( $P \leq 0.05$ ) using the t-test.

For comparison groups:

1. Accentual Eccentric Loading Countermovement Jumps and Drop Jump Training with Ladder Training
2. Ladder Training Alone

the Mann-Whitney U test will be used to determine significance and The mean, median, upper quartile and lower quartile will be used to characterize the variables in non-normal data. Frequent (N) and percentage (%) will summarize categorical variables. Chi-square analysis will be utilized to examine efficacy over categorical variables.

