### Alternative Hypothesis(ha)

H1-there will be significant effect of accentual eccentric loading countermovement jumps and drop jump training with ladder training vs ladder training alone on sprint performance and change of direction ability in futsal players: a randomized controlled trial

H2-there will be significant difference between effect of accentual eccentric loading countermovement jumps and drop jump training with ladder training vs ladder training alone on sprint performance and change of direction ability in futsal players: a randomized controlled trial

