## **VIII. Objectives of the study:**

- To evaluate the effect of ladder training on sprint performance and change of direction ability in futsal players.
- To evaluate the effect of accentuated eccentric loading cmj, drop jump training with ladder training on sprint performance and change of direction ability in futsal players.
- To compare the effect of accentuated eccentric loading countermovement jumps and drop jump training with ladder training vs ladder training alone on sprint performance and change of direction ability in futsal players.

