## **IX. Methodology:**

**Study type:** Experimental study

**Study design:** Randomised controlled trial (RCT)

**Target population:** Futsal players

**Sampling technique:** Simple random sampling

**Duration of study:** 1 year

**Allocation ratio:** 1:1

**Blinding:** Single blinded (participants will be blinded)

**Study setting :** futsal turfs across dmiher , Sawangi Meghe Wardha

**Study population:** recreational and competitive futsal players

**Sample size:** the sample size for this study was determined using g\*power (version 3.1.9.4, heinrich heine universität düsseldorf, düsseldorf, germany), a statistical software that facilitates power analysis and sample size estimation based on various statistical tests.

formula using mean difference

$$n1 = n2 = 2 \times [(z\alpha + z\beta)^2 \times \sigma^2] / (\delta^2)$$

Where:

- $Z\alpha = 1.96$  (considering ci at 95%)
- $Z\beta = 1.64$  (power at 95%)

**Primary variable:** 30 m sprint

- Mean  $\pm$  sd (pre) result on 30 m sprint in tbi readings =  $4.36 \pm 0.12$
- Mean  $\pm$  sd (post) result on 30 m sprint in tbi readings =  $4.29 \pm 0.13$
- Mean difference ( $\delta$ ) = 0.064
- Pooled standard deviation = 0.125

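### The protocol names one primary outcome for sizing but two for analysis, and does not say whether success on either or on both is required

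*Protocol*

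**What the plan says.** Three places in the protocol define what is primary.

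- **Section IX, Methodology (sample size):** "Primary variable: 30 m sprint". The means, standard deviations and difference used for sizing all belong to the sprint. No effect size or standard deviation for the agility T-test appears anywhere.
- **Section XVI, Outcome measures:** a heading in the singular for the primary outcome, with both the sprint and the T-test under it.
- **Section XVII.3, Statistical method:** under "Outcome variables: Primary outcomes" the list reads "30 Meter Sprint Test" and then "2. Agility T-Test", with no ranking beyond the numbering. On the level: "The significant difference will be at a 5% level". No split of that level, testing order or success rule is given.

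The tests named are the t-test and, for non-normal data, the Mann-Whitney U test between the two groups. No paired or other within-arm test is named.

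Section VIII has three objectives. The first is "To evaluate the effect of ladder training on sprint performance and change of direction ability in futsal players", the second does the same for the combined programme, and the between-group comparison comes third.

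**The concern.** With one primary outcome, a 5% test means a 5% chance of a false positive conclusion. With two, the chance depends on how they are combined, and the protocol leaves that open. A reader of section IX would expect the trial to stand or fall on the sprint. A reader of section XVII.3 could accept a significant T-test in its place. If that choice is made after the data are seen, the 5% level no longer describes the trial's conclusion.

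A second, smaller matter concerns objectives 1 and 2. Both arms receive ladder training and there is no untrained arm. An improvement within one arm may therefore reflect familiarity with the test or conditioning over the season. Objective 1 cannot be answered by the randomised comparison at all, because ladder training is common to both arms.

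**Working it through.** **1. The sizing rests on the sprint alone.** Inputs from section IX: z values 1.96 and 1.64, SD 0.125, difference 0.064 s. The protocol's formula gives

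2 × (1.96 + 1.64)² × 0.125² / 0.064² = 2 × 12.96 × 0.015625 / 0.004096 = 98.9, so 99 per group.

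The stated figure of 28 per group is not reproduced. That is a separate fault, to be corrected whichever rule is chosen here. For the present point, no T-test quantity enters the calculation.

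**2. Either outcome suffices.** Two between-group tests, each two-sided at 5%, with no true difference on either outcome.

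- Independent outcomes: 1 − 0.95² = 0.0975.
- Upper bound for any dependence: 0.05 + 0.05 = 0.10.
- Correlated outcomes: 1 − P(|Z₁| ≤ 1.96 and |Z₂| ≤ 1.96), with (Z₁, Z₂) bivariate normal with correlation r. The protocol gives no r, so a range is assumed.

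| Assumed r | Familywise error |
|---|---|
| 0 | 9.75% |
| 0.5 | 9.1% |
| 0.7 | 8.3% |
| 0.9 | 7.0% |

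**3. Both must succeed.** A false claim requires rejecting at least one true null hypothesis at 5%, so the error is at most 5% without adjustment. If both nulls are true and the outcomes independent, it is 0.05² = 0.25%.

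**4. Sprint first, T-test only if the sprint is significant.** If the sprint null is true, any false claim must begin with a false sprint rejection, at most 5%. If the sprint null is false, the only possible false claim is on the T-test, at most 5%. The familywise error is at most 5% in every case.

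**5. Both primary, level divided.** At 0.025 each, the error is 1 − 0.975² = 4.94% if independent, and at most 5% otherwise. On the sprint inputs with 95% power, 2 × (2.241 + 1.645)² × 0.125² / 0.064² gives 116 per group, against 100 at the 5% level with unrounded z values. Holm starts from the same 0.025 step, so 116 is a cautious figure for it.

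**6. Why a within-arm change is weak evidence (illustration only).** Take the section IX figures: SDs 0.12 and 0.13, change 0.064 s, 28 in an arm. Suppose the same change occurs in both arms, so that they do not differ. The SD of the change is √(0.12² + 0.13² − 2r × 0.12 × 0.13), where r is now an assumed pre-post correlation. At r = 0.5 this is 0.125. The standard error is 0.125/√28 = 0.0237, and 0.064/0.0237 is about 2.70. A paired test would then be significant with probability about 77%. At r = 0.7 the figure is about 94%, and at r = 0.9 over 99%.

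**The case against.** The strongest reply is that no excess error is shown. The hypotheses and objectives join sprint performance and change of direction with the word and. If that means both must succeed, the error is at most 5%. A multiplicity rule may also stand in a statistical analysis plan that is not at hand, and sizing on one of two primary outcomes is not wrong in itself.

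Much of this stands. A reader might infer that the false positive rate certainly exceeds 5%. The protocol does not support that, because it never says that either outcome suffices. But the joint wording is not a decision rule either, and the conflict between one primary variable and two primary outcomes lies within the protocol. An analysis plan could add a rule, but the conflicting sections would still need correction.

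A reader might also go further, take H1 as a within-arm hypothesis, count six tests (two between groups, four within arms) and reach an error of about 26%. The documents do not support that for three reasons:

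- H1 opens "there will be significant effect of accentual eccentric loading countermovement jumps" but goes on to name ladder training alone as the comparator, so it reads as a loose near-duplicate of H2.
- The statistical section names no within-arm test.
- The six tests would not be independent, since a between-group difference in change is built from the two within-arm changes.

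Nor is regression to the mean a strong argument, because the entry criteria do not select on test performance.

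**Conclusion.** The protocol contradicts itself on the number of primary outcomes and leaves the success rule unstated. The consequence is conditional: about 7% to 10% familywise error if either outcome can carry the claim, over the assumed correlations of 0 to 0.9, and at most 5% if both must succeed. These figures assume two-sided tests at 5% and approximately normal test statistics.

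The within-arm objectives are a matter of interpretation and add nothing to this error count. A genuine change over six weeks is not a false positive, but without an untrained comparator it cannot be credited to training.

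**What to change.** Reconcile sections IX, XVI and XVII.3 before any outcome data are seen.

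- **Preferred:** name the between-group comparison of 30 m sprint time as the single primary test at 5%, as the sizing already does. Make the agility T-test the key secondary outcome, tested at 5% only if the sprint comparison is significant.
- **If both are to stay primary:** either apply Holm, or state that both must be significant for the trial to be positive.
- **Objectives 1 and 2:** reword as description of each arm, with mean change and 95% confidence interval, and no claim of a training effect.

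The preferred option costs only wording and adds no participants for multiplicity. Its downside is that a T-test result cannot be claimed as confirmatory if the sprint comparison fails. Keeping both primary costs more. Holm would need up to 116 per group on the protocol's sprint inputs. A both-must-succeed rule lowers power by an amount that cannot be computed until an effect size and SD for the T-test are supplied.

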**Minimum sample size required**

$$N1 = n2 = 2 \times [(1.96 + 1.64)^2 \times (0.125)^2] / (0.064)^2 = 28 \text{ per group.}$$

Considering a 10% dropout rate:

- Dropout = 10%
- **Total sample size required = 62.**

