### **XIV. Procedure:**

Participants will be screened based on the inclusion and exclusion criteria. Individuals meeting the inclusion criteria will be recruited for the study after being informed about the purpose and nature of the study. Written informed consent will be obtained from all participants. Participants will then be randomly divided into two groups: group a and group b, with equal participants in each group.

Before the intervention, both groups will undergo baseline assessments for sprint performance and change of direction (cod) ability. Once baseline testing is completed, participants will receive their respective interventions as described below:

- Group A: Accentuated eccentric loading (AEL) countermovement jumps, drop jump training with ladder training.
- Group B: Ladder training only.

Group A will receive accentuated eccentric loading (AEL) countermovement jumps and drop jump training with ladder training and Group B will receive Ladder training.

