## **XVII. Data collection, management, and analysis**

### **1. Data collection methods**

Pre-intervention data will be collected upon enrolment; additional post-intervention data will be collected after 6 weeks of the intervention.

|                                    |           | Study period |                                                                                      |       |       |       |       |       |           |
|------------------------------------|-----------|--------------|--------------------------------------------------------------------------------------|-------|-------|-------|-------|-------|-----------|
|                                    | Enrolment | Allocation   | Post-allocation                                                                      |       |       |       |       |       | Close-out |
| Timepoint**                        | $-t_1$    | 0            | $T_1$                                                                                | $T_2$ | $T_3$ | $T_4$ | $T_5$ | $T_6$ | $T_x$     |
| Enrolment:                  |           |              |                                                                                      |       |       |       |       |       |           |
| Eligibility screen                 | X         |              |                                                                                      |       |       |       |       |       |           |
| Informed consent                   | X         |              |                                                                                      |       |       |       |       |       |           |
| [list other procedures]     | X         |              |                                                                                      |       |       |       |       |       |           |
| Allocation                         |           | X            |                                                                                      |       |       |       |       |       |           |
| Interventions:              |           |              |                                                                                      |       |       |       |       |       |           |
| [intervention a]            |           |              | [figure not shown] |       |       |       |       |       |           |

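### The protocol picks the between-group test by a normality pre-test, names no baseline adjustment and does not say whether post values or changes are compared; one fixed ANCOVA per outcome would settle all three at no cost

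*Protocol*

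**What the plan says.** The analysis is set out in the Protocol, section XVII, Statistical method, under Outcome variables: Primary outcomes. The 30 m sprint and the agility T-test are both listed as primary. All continuous outcomes are first tested for normality with the Kolmogorov-Smirnov test, and "Non-parametric tests will be used to assess significance if the null hypothesis of normality is rejected". Significance is otherwise judged at the 5% level with a t-test. For the comparison of the two training groups with non-normal data, "the Mann-Whitney U test will be used to determine significance".

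The section names no covariate and no baseline adjustment. It does not say whether the quantity compared is the post-training time or the change from baseline.

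Baseline data will exist. Under Procedure, "both groups will undergo baseline assessments for sprint performance and change of direction (cod) ability", and under Data collection methods, "additional post-intervention data will be collected after 6 weeks of the intervention". Annexure II has a Pre and a Post column for each test, and a field for sex.

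The sample-size text in Methodology uses a difference of 0.064 s, taken from pre and post readings, with "Pooled standard deviation = 0.125". It arrives at 28 per group and, after dropout, "Total sample size required = 62".

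**The concern.** Three things are left open or fixed badly.

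- **The quantity analysed.** A t-test on post-training times and a t-test on changes are different analyses with different precision, and the text permits either.
- **The type of result.** The pre-test lets the observed data decide whether a primary outcome is reported as a difference in mean seconds or as a rank comparison. The two primary outcomes could end up with results of different kinds.
- **Efficiency.** Players differ in speed before they start. The eligibility criteria admit recreational and competitive players, and the data sheet provides for both sexes. A test that names no baseline adjustment carries that between-player variation in its error term or, if changes are used, removes it only in part. Chance imbalance at baseline is realistic with about 62 players under simple randomisation, and nothing in the section deals with it.

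What is at stake is precision and a primary estimate defined in advance. Type I error is not at stake.

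**Working it through.** **Inputs.** From Methodology: difference δ = 0.064 s, SD σ = 0.125 s, z values 1.96 ("considering ci at 95"%, read as two-sided 5%) and 1.64 (95% power), "Allocation ratio: 1:1", and 28 per group. The correlation r between baseline and post-training time is not given. I assume 0.5 to 0.8 and equal SDs at both times. δ and σ are taken at face value as a between-group difference and a between-player SD.

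**The protocol's own figure.** Its formula with its inputs gives 2 × (1.96 + 1.64)² × 0.125² / 0.064² = 98.9, so 99 per group. The stated 28 does not follow. The power figures below therefore start low for a reason separate from this point.

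**Power at 28 per group** (two-sided 5%, noncentral t):

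- Noncentrality = δ / (SD_a × √(2/28)), where SD_a is the SD of the quantity analysed.
- Post values: SD_a = 0.125. Noncentrality = 0.064 / (0.125 × 0.2673) = 1.916, 54 df, power 46.9%, whatever r is.
- Change scores: SD_a = 0.125 × √(2(1 − r)), 54 df.
- ANCOVA: SD_a = 0.125 × √(1 − r²), 53 df.

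| Assumed r | SD, change (s) | Power, change | SD, ANCOVA (s) | Power, ANCOVA | ANCOVA minus post values | ANCOVA minus change |
|---|---|---|---|---|---|---|
| 0.5 | 0.125 | 46.9% | 0.108 | 58.4% | 11.5 points | 11.5 points |
| 0.6 | 0.112 | 55.7% | 0.100 | 65.2% | 18.3 points | 9.5 points |
| 0.7 | 0.097 | 68.0% | 0.089 | 75.0% | 28.1 points | 7.0 points |
| 0.8 | 0.079 | 84.5% | 0.075 | 88.0% | 41.1 points | 3.5 points |

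At r = 0.5 a change score gains nothing over post values. At r = 0.3 it loses: 36%, against 47% for post values and about 51% for ANCOVA.

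**Can adjustment rescue 28 per group?** Setting 98.9 × (1 − r²) = 28 gives r² = 0.717, so r ≈ 0.85. Below that, ANCOVA does not reach the stated 95%.

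**The pre-test on normal data.** In 6,000 simulated trials with 28 per arm, Kolmogorov-Smirnov with mean and SD estimated from the sample rejected in about 0.02%. The two-stage procedure had type I error 4.8% and power 46.6%, the same as the plain t-test. The pre-test itself costs almost no power here.

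**The pre-test on skewed data.** The answer depends on a version the protocol does not specify. For single lognormal samples of 28 with log-SD 0.3 and 0.5, the uncorrected test rejects roughly 0.4% and 3%; with the Lilliefors correction, roughly 20% and 45%. This skew is far beyond what the protocol's figures suggest: 0.125 / 4.36 is a coefficient of variation of about 3%.

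**The case against.** **The protocol may already use the baseline.** A t-test on change is a plausible reading: both time points are recorded, and the sample-size text works from a pre-to-post difference. This stands. A reader might infer that the plan ignores the baseline times and so gives away much of its power, but the text does not support that. It does not state what is compared. If changes are compared, the gain from ANCOVA is about 4 to 12 points over the assumed range, not 12 to 41.

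**The low power belongs to the sample size.** This also stands. At 99 per group the unadjusted post-value t-test has about 95% power, and ANCOVA adds little (98.5% at r = 0.5).

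**The pre-test is harmless in practice.** On power with normal data, that is right. A reader might also infer that the Kolmogorov-Smirnov test is useless as a safeguard because it almost never rejects. That holds only for the uncorrected version, which the protocol does not specify, and was shown on implausibly skewed data. What remains is that the rule makes the type of primary result depend on the data. If the test rarely rejects, the practical consequence is small.

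**An unadjusted test is valid, and covariates may be left to a statistical analysis plan.** The first part is true. On the second, a list of covariates could well sit in a plan not shown here. But this protocol itself fixes the test and the rule for choosing it, and that rule is what should change.

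**Conclusion.** The point holds as a free improvement, not as an error that invalidates the analysis. Three facts rest on the text alone: the test is chosen by a normality pre-test, no baseline adjustment is named, and the compared quantity is not stated.

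The size depends on the unstated correlation and on which reading is meant. For r from 0.5 to 0.8 at 28 per group, ANCOVA gains about 12 to 41 points of power over post values, or about 4 to 12 over change scores. It is the most powerful of the three throughout that range, so the recommendation does not depend on which reading was intended. The loss comes from not adjusting, not from the pre-test. Adjustment does not make 28 per group adequate unless r is about 0.85, so the sample-size calculation needs its own correction.

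**What to change.** In section XVII, Outcome variables: Primary outcomes, delete the Kolmogorov-Smirnov test as a selector and state one primary analysis for each outcome: a linear model (ANCOVA) of the week-6 time on training group and the baseline time of the same test, reporting the adjusted group difference in seconds with its 95% CI. Sex, already on the data sheet, may be added as a covariate if this is fixed in advance. Keep the Mann-Whitney U test, or a permutation test, as a sensitivity analysis that does not replace the primary result.

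The cost is a few sentences in one section. No new measurement, visit or participant is needed. The sample-size calculation should be corrected separately; any credit taken there for baseline adjustment should state the correlation assumed and its source.

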### **Methods monitoring**

Data monitoring: The data will be monitored by the data monitoring committee of Ravi Nair Physiotherapy College.

Harms:

Any episode of the adverse events shall be reported to the ethical committee and the clinician in charge for assessing and managing the solicited and spontaneous adverse events and other unintended effects of trial interventions or trial conduct.

